## Methods/Design

### Trial design

This study is a randomized controlled trial. It follows a waitlist control, single-blinded (participants and psychologists who conduct the group-based CBT are not blinded and the assessors of all measures are blinded) design. The allocation of participants will be equal (1:1) across a CBT group (intervention group) and a waitlist control group. All assessment will be administrated by the blinded assessors at the enrolment, post-intervention, and at 12 weeks follow-up. The entire trial design is illustrated in Figure 1. First, an assessment for eligibility will be performed. For individuals who meet the inclusion criteria, a pre-assessment will be performed no more than 4 weeks before the treatment. After pre-assessment, participants will be allocated into the immediate treatment condition or the waitlist condition. After the completion of treatment, post-assessment will be performed within 4 weeks. After an additional 12 weeks, a follow-up assessment will be performed. The pre-assessment and intervention will be conducted at the Department of Child and Adolescent Mental Health, the National Institute of Mental Health, National Center of Neurology and Psychiatry, and the Department of Child Psychiatry, the University of Tokyo Hospital. The allocation and post- and follow-up assessments will be conducted at the Department of Child Psychiatry, the University of Tokyo Hospital.

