### Randomization

Enrollment and random allocation will be performed through central registration at the University Hospital Clinical Trial Alliance Clinical Research Supporting System (UHCT ACReSS) at the University of Tokyo. A minimization method will be used with sex as the allocation factor. A third party, who is not involved in this trial, will enroll participants after examining their eligibility and informed consent. Owing to allocation concealment, the random allocation sequence will be provided by UHCT ACReSS and will not be revealed to any researchers or staff until the end of the enrollment period. As this is a single-blinded trial, all assessments will be conducted by raters without knowledge of whether the participant is in the CBT or waitlist conditions.

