### Statistical methods

All analyses will be performed using SPSS 20 J (SPSS Inc., Chicago, IL, USA). All data will be analyzed under the intent-to-treat principle. For the primary outcomes, independent *t*-tests will be used to compare changes in scores between the pre-assessment and post-assessment periods between the CBT group and the waitlist control group. The primary outcomes will be analyzed controlling for potential confounds (for example, age, gender, IQ, and clinical characteristics) using regression models. Secondary outcomes will be analyzed using relevant tests at each assessment, controlling for possible confounds as described above. Subgroup analyses will be performed for any possible confounds to differentiate the efficacy of CBT at follow-up.

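### Baseline site, which differs between participants while later assessments share one place, is neither a minimization factor nor a named covariate; the cost is modest precision and chance imbalance, not bias

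*Protocol article*

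**What the plan says.** The Trial design section of the protocol article sets out an uneven use of sites. "The pre-assessment and intervention will be conducted at the Department of Child and Adolescent Mental Health", and the same sentence adds the Department of Child Psychiatry at the University of Tokyo Hospital as a second place. The next sentence reads "The allocation and post- and follow-up assessments will be conducted at the Department of Child Psychiatry, the University of Tokyo Hospital". On timing it says "After pre-assessment, participants will be allocated into the immediate treatment condition or the waitlist condition", and on the ratio "The allocation of participants will be equal (1:1) across a CBT group (intervention group) and a waitlist control group".

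The Randomization section says "A minimization method will be used with sex as the allocation factor". No other factor is named.

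Under Statistical methods, independent t-tests will "compare changes in scores between the pre-assessment and post-assessment periods between the CBT group and the waitlist control group". The primary outcomes will also be analysed by regression, "controlling for potential confounds (for example, age, gender, IQ, and clinical characteristics"). Site is not in that list, though the list is given by way of example. Secondary outcomes are to be adjusted for the same confounds.

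The end of Assessments/measures adds that the questionnaires are mailed to participants' homes before each assessment date, that the GAF and LSAS are interviews, and that the MPMR is a computer task.

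**The concern.** As written, someone pre-assessed at the national center changes setting, and possibly assessor, before the post-assessment, while someone pre-assessed at the university hospital does not. The primary variable is pre-to-post change, so any effect of that switch becomes part of the outcome. Participants or CBT delivery might also differ between the two departments.

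Nothing in the allocation balances site, and nothing in the named analysis removes it. If site shifts change scores, the shift adds noise to the comparison. If the arms also happen to differ in site mix, it moves the estimate in the trial actually run. With 30 recruited per arm and 25 intended for analysis, there is little precision to spare.

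**Working it through.** **Inputs from the protocol.** 30 recruited per arm (60 in total), 25 per arm intended after dropout; 1:1 allocation; minimization on sex only; allocation after pre-assessment; one post-assessment department for both arms.

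**Assumptions, not in the protocol.** Half the participants at each pre-assessment site; a site shift δ in the change score of 0.5 within-site SD, range 0.3 to 0.8; two-sided alpha 0.05; sex minimization ignored. The protocol has no figure of its own on this point to reproduce.

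**1. Is there expected bias?** Pre-assessment site is fixed before random allocation, so arm cannot determine it, and post-assessment is in the same place for both arms. The expected site contribution to the contrast is 0. In simulation (20,000 runs per setting, 30 per arm) the mean estimate stayed within 0.005 SD of the truth for shifts of 0 to 1.0 SD. Type I error of the unadjusted t-test was 0.048 to 0.052.

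**2. How large can chance imbalance be?** With independent site mix in each arm, the SD of the difference in site share is √(2 × 0.25/30) = 0.129. The 95th percentile of its absolute value is 8/30 = 0.267, and the chance of at least 20 points is 0.16. With the site totals held fixed, the SD is (2/30) × √(30 × 0.25 × 30/59) = 0.130, the 95% limit is 1.96 × 0.130 = 0.255, and the chance of at least 20 points is 0.20. The two SDs agree; the probabilities differ because the possible differences are spaced differently.

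**3. What does that do to the contrast?** Shift = imbalance × δ, against a standard error of √(2/30) = 0.258 SD.

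| δ (SD) | 0.267 × δ (SD) |
|---|---|
| 0.3 | 0.08 |
| 0.5 | 0.13 |
| 0.8 | 0.21 |

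With site totals fixed and δ = 0.5, the shift at the 95% limit is 0.255 × 0.5 = 0.13 SD. With 25 per arm it is 0.14 SD (standard error 0.283). If only 20% come from the second site, with 30 per arm, it is 0.10 SD.

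Given an imbalance of at least 20 points in one direction (about a 10% chance), type I error of the unadjusted test was 0.068 at δ = 0.5, 0.082 at 0.8 and 0.104 at 1.0.

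**4. What does adjustment save?** A regression on arm, pre-assessment score and sex leaves 60 − 4 = 56 residual degrees of freedom; adding site leaves 55. The ratio of adjusted to unadjusted variance is 1/(1 + 0.25δ²) × 56/55.

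- δ = 0.3: 0.978 × 1.018 = 1.00, no saving.
- δ = 0.5: 0.941 × 1.018 = 0.96, about 4%.
- δ = 0.8: 0.862 × 1.018 = 0.88, about 12%.

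**5. Power.** For an assumed treatment effect of 0.75 SD, with 30 per arm and half at each site:

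| δ (SD) | t-test | with site term |
|---|---|---|
| 0 | 0.81 | 0.81 |
| 0.5 | 0.79 | 0.81 |
| 0.8 | 0.76 | 0.80 |
| 1.0 | 0.72 | 0.81 |

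If site has no effect, the site term costs less than 0.01 in power (0.813 against 0.806).

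**6. Which outcomes?** The TAS-20, CISS and ASD questionnaire are completed on forms mailed home, so a change of assessment place has no evident route into them. The MPMR (primary) and the GAF and LSAS (secondary) are administered at the assessment.

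**The case against.** A reader might infer that the site layout biases the treatment effect. It does not: step 1 shows no expected shift and no inflation of unconditional type I error. What remains is the chance imbalance that any randomized trial carries for a factor it does not balance, and the t-test's standard error already allows for it on average. This part of the objection stands in full.

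A reader might also infer that the protocol rules out adjustment for site. The covariate list is illustrative, and an analysis plan that is not shown may name site. All that can be said is that site is not named. It is also too much to say that every primary outcome is exposed to the change of setting, since three of the four are mailed questionnaires. The fourth is scored as percentage correct on a computer, which leaves little room for assessor judgement.

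The size is fairly questioned too. Recruitment runs through the university hospital and its web site, so an even split is unsupported, and it is the split that gives the largest imbalance. The 0.5 SD shift has no source. Finally, the waitlist arm has no CBT before post-assessment, so a difference in delivery between sites would be a treatment-by-site interaction, which a site main effect does not remove.

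These objections narrow the point without removing it. The protocol itself fixes sex as the only minimization factor and an unadjusted change-score test as the primary comparison in a design with two baseline sites. A pre-specified site term improves on that stated choice at almost no cost.

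**Conclusion.** The point holds as a minor, inexpensive improvement. The arrangement of sites, the single minimization factor and the unadjusted primary test are as described. The consequence is lost precision and exposure to chance site imbalance, chiefly for the MPMR, GAF and LSAS. The mailed outcomes are touched only if participants or delivery differ by site.

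Under a 50/50 split and a 0.5 SD site shift, a 95th-percentile imbalance moves the contrast by about 0.13 SD, roughly half a standard error (0.13/0.258), and adjustment saves about 4% of variance. Over shifts of 0.3 to 0.8 SD the ranges are 0.08 to 0.21 SD and 0 to 12%. Both the split and the shift are assumptions, and the true effect could be nil.

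**What to change.** Under Statistical methods, before any analysis, replace the unadjusted change-score t-test as the reported primary analysis with a regression of the post-assessment score on arm, pre-assessment score, sex (the minimization factor) and pre-assessment site. Define the site term by where the pre-assessment was done, because the protocol does not say that CBT is always given in the same place. As secondary outcomes are already to be adjusted for the same confounds, naming site there also covers the GAF and LSAS.

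The cost is a line or two of wording, a few degrees of freedom, and a check that pre-assessment site is recorded for each participant, which the protocol does not state. Changing the minimization is not worth proposing: Trial status reports 88% already included, leaving about 0.12 × 60 = 7 participants.

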**Figure 1 F1:**
[figure not shown]
**CONSORT flow chart of the clinical trial.** The allocation of participants will be equal (1:1) across a cognitive-behavioral therapy group and a waitlist control group. All assessment will be administrated at the enrolment, post-intervention, and at 12 weeks follow-up. Both pre- and post-assessment will be performed at 4 weeks before or after the treatment.

The target sample size is 60, and registration began on September 1, 2011. This trial was registered in the University Hospital Medical Information Network Clinical Trials Registry and approved by the International Committee of Medical Journal Editors (No. UMIN000006236).

### Ethical consideration

The Ethics Committee of the National Institute of Neurology and Psychiatry (No. A2010-022) and Graduate School of Medicine and Faculty of Medicine at the University of Tokyo have approved the study protocol (No. 2702). All participants will be asked to sign a written informed consent, as approved by the ethical committee of each site, according to the Declaration of Helsinki after receiving a complete explanation of the trial.

### Participants

The participants will be individuals diagnosed with pervasive developmental disorder based on the text revision of the diagnostic and statistical manual of mental disorders, fourth edition (DSM-IV-TR) criteria [18]. In our study, the Cat-kit [16], which was used in the studies of Sofronoff and colleagues, will be used, along with the procedure of those studies. Sofronoff and colleagues had 23 to 25 participants in each of their intervention groups. Therefore we decided to use 25 participants each for the intervention and control groups, recruiting 30 individuals per group to account for potential dropouts.

The inclusion criteria are as follows: (1) age between 18 and 50 years; (2) a full intelligence quotient (IQ) of at least 85 and a verbal IQ of 100 or above (IQ will be evaluated using the Wechsler Adult Intelligence Scale, Third Edition [19]); (3) a specific diagnosis based on the Autism Diagnostic Schedule (ADOS) [20] or the Autism Diagnostic Interview, Revised (ADI-R) [21] with a score above the ASD cut-off; (4) high school graduate or above; (5) knowledge of one’s diagnosis, (6) realization of one’s poor emotional self-awareness/ability to express emotion and poor understanding of others’ emotions and thoughts, and (7) willingness to participate. Individuals with a comorbid psychiatric and/or unstable condition will be excluded (Table 1). The Mini-International Neuropsychiatric Interview [22] will be used to evaluate psychiatric co-morbidity. Any individual who fails to attend more than three sessions will be regarded as 'dropping out', but supplementary instruction will be regarded as equivalent to attendance and will be offered up to three times. Current medication doses should not be increased greatly during the trial. Furthermore, current individual psychological therapy and regular medical treatment will be continued during the intervention. A detailed ASD assessment and diagnosis will be carried out for all intervention candidates. Recruitment of individuals with an ASD diagnosis will be conducted through the Department of Child Psychiatry or Neuropsychiatry at the University of Tokyo Hospital or an advertisement on the University of Tokyo Hospital web site.

**Table 1 T1:** All measures assessed at enrollment, pre-intervention, post-intervention, and follow-up, including primary and secondary outcomes

**Measures**	**Time required (minutes)**	**Dx data**	**Pre-intervention**	**Post-intervention**	**Follow-up**
DSM-IV-TR		○			
M.I.N.I	30		○		
WAIS-III	60	○			
AQ	10	○			
E-SQ	15	○			
ADI-R	(120: parent)	○			
ADOS	90	○			
SRS-A	15	○			
SCQ	(20: parent)	○			
MPMR	15		○	○	○
TAS-20	5		○	○	○
CISS	10		○	○	○
ASD	5		○	○	○
Questionnaire					
WHO-QOL26	10		○	○	○
GAF	30		○	○	○
STAI	10		○	○	○
SPAI	25		○	○	○
LSAS	10		○	○	○
CES-D	5		○	○	○

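### ITT is promised, but dropping out is defined only by missed CBT sessions and the primary change-score t-test needs both scores: state the analysis set and use a baseline-adjusted model

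*Protocol article*

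**What the plan says.** Four statements in the protocol article bear on this point.

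- Statistical methods sets the principle: "All data will be analyzed under the intent-to-treat principle".
- Participants gives the only definition of dropping out: "Any individual who fails to attend more than three sessions will be regarded as" a drop-out. It adds that "supplementary instruction will be regarded as equivalent to attendance and will be offered up to three times".
- Participants also sets the size: "Therefore we decided to use 25 participants each for the intervention and control groups, recruiting 30 individuals per group to account for potential dropouts". The 25 comes from earlier child studies, which had "23 to 25 participants in each of their intervention groups".
- Statistical methods gives the primary test. Independent t-tests "will be used to compare changes in scores between the pre-assessment and post-assessment periods between the CBT group and the waitlist control group". Regression models controlling for possible confounders follow. Their examples include age, gender and IQ, and the baseline value of the outcome is not named.

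The comparator is a waitlist (Trial design), the eight weekly sessions belong to the CBT group (Details of the intervention program), and the minimization factor is sex (Randomization).

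**The concern.** Under ITT, someone who skips sessions but gives a post-intervention score is a non-adherent participant who still counts. The article uses the word for leaving a trial for such a person, and uses the same word to justify recruiting five more per arm. It never says whether these people are still assessed, or in which set they are analysed.

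That matters because the definition works on one side only. Before the post-assessment, waitlist participants have no sessions to miss. An analysis set built on attendance would therefore keep the more engaged CBT participants and compare them with an unselected control arm. If poor attenders do worse, the comparison leans toward CBT.

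A second weakness lies in the test itself. A change score exists only where both values exist. The t-test therefore drops anyone without a post score unless values are imputed, even if that person gave a follow-up score. It also leaves unused the baseline score as a covariate and the factor on which allocation was balanced.

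**Working it through.** **1. The plan's own figure.** Inputs from Participants: 25 wanted and 30 recruited per arm. The implied allowance is (30 − 25)/30 = 5/30 = 16.7%. Check: 25/(1 − 5/30) = 30 per arm, 60 in total, which matches "The target sample size is 60" and the equal allocation in Trial design. No drop-out rate is stated, so 16.7% is back-calculated and this shows internal consistency only.

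**2. Who can meet the definition.** CBT arm: eight sessions, so yes. Waitlist arm before the post-assessment: no sessions, so no. The allowance is nevertheless the same in both arms, so it cannot rest on missed sessions alone. The article uses one word for two different things.

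**3. Shift if CBT poor attenders were left out (conditional).** Suppose k of 30 are omitted from the CBT arm and would have ended g SD worse than the other CBT participants. The mean of those kept exceeds the full-arm mean by (k/30) × g. The gap g is assumed; the article gives no figure. With k = 5:

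- g = 0.3: (5/30) × 0.3 = 0.05 SD
- g = 0.5: (5/30) × 0.5 = 0.08 SD
- g = 0.8: (5/30) × 0.8 = 0.13 SD

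With no true effect and a normal approximation at 25 v 30, a gap of 0.5 SD takes the nominal 5% two-sided error to about 6%. A gap of 1.0 SD (shift 0.17 SD) takes it to about 9%. With k = 2 the same two gaps give 5.2% and 5.7%; with k = 8 they give about 8% and 16%.

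**4. Precision.** The standard error is proportional to √(1/n₁ + 1/n₂), here relative to 30 v 30.

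- Five lost from CBT only (25 v 30): √[(1/25 + 1/30)/(2/30)] = √1.10 = 1.049, about 5% wider.
- Five lost from each arm (25 v 25): √[(2/25)/(2/30)] = √1.20 = 1.095, about 10% wider.

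Assuming 80% power and a two-sided 5% level, the detectable difference is 0.74 SD at 30 v 30, 0.77 SD at 25 v 30 and 0.81 SD at 25 v 25.

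**5. Data used by each method.**

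- Change-score t-test: needs pre and post scores. Someone with pre and follow-up scores but no post score contributes nothing.
- Likelihood-based repeated-measures model of post and follow-up scores, with baseline score and sex as covariates: that same person contributes through the correlation between visits. With complete data, its contrast at post is essentially ANCOVA.
- Neither method uses someone with no score after baseline.

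**The case against.** A reader might infer that the plan excludes poor attenders, that it therefore breaks ITT in one arm, and that the t-test is prescribed as a deletion rule. The documents do not support this.

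- No sentence says that poor attenders stop being assessed, are excluded or are replaced. The only rule on who is analysed is the ITT sentence, and the assessment schedule carries no attendance condition.
- Recruiting 30 to end with 25 is ordinary allowance for missing outcomes and is compatible with ITT. Because the allowance also covers the waitlist arm, it must include ordinary loss to assessment.
- The article does not say how missing scores are handled. Such rules are commonly left to the SAP or full protocol, neither of which is shown, and imputed values could enter the same t-test.
- A covariate-adjusted regression is also planned. If loss depended only on covariates in that model, a complete-case fit need not be biased.
- A shift of 0.05 to 0.13 SD is small beside a detectable difference of 0.74 SD.

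All of this stands, and it makes the bias conditional. It does not remove the mismatch, because the attendance-based label, the use of drop-outs in sizing the trial and the ITT promise are all in the published text and are not connected. Nor does it defend the choice of test: the planned regression names neither the baseline score nor the follow-up score as a source of information.

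**Conclusion.** The point holds as an ambiguity in the analysis set together with a weak choice of primary test. It is not shown that the trial departs from ITT.

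The article promises ITT but defines dropping out only by missed sessions, which before the primary comparison can happen only in the CBT arm. That invites an attendance-based set without prescribing one. If the invitation were taken up for 5 of 30 CBT participants with a gap of 0.3 to 0.8 SD, the effect would shift by about 0.05 to 0.13 SD toward CBT and the standard error would widen by about 5%. The 10% figure applies only if five are lost in each arm. The number left out and the gap are assumptions; five is simply the plan's own allowance.

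Independently of that, the change-score t-test is complete-case unless imputation is added, and it uses neither baseline score nor sex as a covariate. A better analysis is available from scores the trial already collects.

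**What to change.** 1. **Primary analysis.** For each primary outcome, replace the t-test on change with a likelihood-based repeated-measures model of the post and follow-up scores. Adjust for baseline score and sex, let the arm effect differ by visit, and take the post contrast as primary. Analyse everyone in the randomized arm.
2. **Wording.** Reconcile Participants with Statistical methods. Call missed sessions non-adherence, and state that such participants stay in the assessment schedule and in their randomized arm. Reserve drop-out for loss to assessment. The attendance threshold can be read as missing more than three sessions or as attending three or fewer; say which is meant.
3. **Attendance-based analysis.** If one is wanted, name it as supportive only.

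The cost is slightly more analysis work, revised wording, and some effort to follow up people who stop attending. No new measure is needed. Two limits should be stated openly. Trial status reports 88% of participants included and 68% of those tested at follow-up. If the 88% refers to the target of 60, that is about 0.88 × 60 = 53 included and 0.68 × 53 = 36 already followed up, so assessments whose window has passed cannot be recovered. Keeping non-attenders also dilutes the effect: if 5 of 30 gained nothing, a 0.80 SD effect in attenders would become 0.80 × 25/30 = 0.67 SD. That is the effect ITT is meant to estimate.
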